### Randomization Procedure

Eligible participants will be randomly designated to either the test group or the control group in a 1:1 distribution ratio. First, all enrolled patients were tested the molecular profile of the tumors, such as HER2, PDL1, MSI and MMR expression. And after the patient underwent molecular profile testing, patients with HER2-positive advanced gastric cancer were excluded since trastuzumab in combination with chemotherapy has become the standard treatment for these patients. For the rest of the other patients, follow up treatment protocols could be adjusted according to the patients’ molecular profile, such as immunotherapeutic antibody PD-1 or PD-L1, and so on. Accordingly, in the statistical analysis of data, different patients also need to conduct subgroup hierarchical analysis according to the molecular detection results of tumors to reduce data error. Biostatisticians not involved in this study will use SAS software 9.2 (SAS Institute, Cary, NC, USA) to generate random sequences. A research assistant not participating in the recruitment process will seal the random list in sequentially numbered nontransparent envelopes stored in a cabinet that is double-locked. The research assistant will store the randomly assigned envelopes separately. Data collection and data analysis will be blinded, except that the intervention is not blinded to participants and clinicians (16).

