### Clinical Data

Clinical data from the patients will be obtained by medical staff and recorded on an online electronic platform (http://www.medresman.org.cn) and in the CRF table. The samples will be coded, and the patients’ identity will be known only by the attending physician. The clinical data will include the following: general patient information, past medical history, past surgical history, laboratory examination results, imaging results, surgery details, PFS and OS. The timing and processing of the above recorded contents will be reflected in the CRF table, and the laboratory examinations will mainly assess preoperative and postoperative routine blood, liver function, tumor markers, and inflammatory indicators. The prognosis of GC with liver metastasis (GCLM) was very poor, with a 5-year survival rate of <10% (17). Patients will be assessed at least monthly from baseline for adverse events *via* verbal interview, physical examination, and blood tests, including a complete blood cell count and assessments of liver and renal function, until disease progression. Abdominal CT and measurements of tumor markers, such as carcinoembryonic antigen, carbohydrate antigen 199, carbohydrate antigen 125, carbohydrate antigen 153 and alpha fetoprotein, were done every 3 months.

A detailed description of the above data is shown in the CRF table. **Table 3** shows the test and data acquisition schedule for this experiment.

**Table 3 T3:** The test and data acquisition schedule for this experiment.

Stage	Pre-operation	Intra-operation	Postoperation					Unplanned follow-up
Follow up period	14-1 days		0-12 month	13-24 month	25-36 month	37-48 month	49-60 month	
Baseline data collected	√	—	—	—	—	—	—	—
Inclusion and exclusion	√	—	—	—	—	—	—	—
Sign informed consent	√	—	—	—	—	—	—	—
Group determination	√	—	—	—	—	—	—	—
Fill in the basic information	√	—	—	—	—	—	—	—
Physical examination	√	—	√	√	√	√	√	—
Imaging examination	√	—	√	√	√	√	√	if necessary
Laboratory examination	√	—	√	√	√	√	√	—
Operation information	—	√	—	—	—	—	—	—
Postoperative pathology	—	√	—	—	—	—	—	if necessary
Safety observation	√	—	√	√	√	√	√	if necessary
Record adverse events	√	—	√	√	√	√	√	if necessary
Other works	√	√	√	√	√	√	√	if necessary

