### Evaluation of Technology Effectiveness

Contrast enhanced CT and tumor marker testing were performed in the first month after D2 gastrectomy and RFA treatment to evaluate the effectiveness of the technique and as a new baseline for future comparison. Every 2 to 4 months, additional CT examinations were performed to assess the progression of the disease. For patients who cannot be evaluated by enhanced CT, additional Hepatic contrast-enhanced ultrasonography, MRI or PET/CT can be used for further evaluation.

For the definition of effective rate of D2 gastrectomy, according to NCCN guidelines for diagnosis and treatment of gastric cancer, tumor clearance effectiveness is defined as that the tumor markers are not increased compared with the baseline data, and CT does not find the recurrence of new tumor or metastatic lymph nodes, or potential metastases in other parts and organs (19, 20).

For the definition of effective rate of RFA treatment, according to standardized terminology and reporting criteria for tumor ablation, technique effectiveness is defined as no evidence of residual tumor within 1 cm of the ablation defect; local tumor progression (LTP) is defined as any new peripheral or nodular enhancement within 1 cm or enlargement of the baseline ablation defect (21, 22).

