Adverse events are adverse medical events that occur after surgical and medical treatment in patients in clinical trials. Adverse events, whether treatment-related or not, will be considered from the date participants sign informed consent until 5 years after the end of treatment in this study. The nature and severity of adverse events will be assessed in accordance with “expert consensus on diagnostic criteria for postoperative complications of gastrointestinal cancer in China”. The investigator will determine if the adverse event is clinically significant, and if so, it will be identified as an adverse event. The investigators will assess possible relationships among the adverse events, the investigational drugs and the surgery to assess adverse events and their causal relationship to treatment. Adverse reactions include those results recorded as positive, correlated, and possibly correlated. The investigators will keep a full record of serious adverse events from the start of the surgery to the end of the study. All serious adverse events will be reported regardless of whether they are related to the use of drugs or surgery in the study. It is the responsibility of the investigators to notify independent ethics committees or governmental regulatory authorities related to adverse events.

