### Follow-up

When patients are discharged from the hospital, the first follow-up is to be performed on the 14th day after surgery. The patients will be given physical examination, imaging examination and laboratory examination to determine the postoperative complications of the patients during the follow-up period. The next chemotherapy plan will be formulated for the patients according to the above results. Physical examination and laboratory examination will be performed at least monthly on all enrolled patients. Imaging examinations will be performed every three months. The patients will be followed up by researchers every month to every 3 months. In addition to the above, the complications of chemotherapy will be examined. Recurrence, metastasis, death, and dates of patients will be recorded. The contents of each follow-up will be collated and combined. The follow-up contents will be recorded in **Table 3**.

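### Data collection is described as blinded, but the printed procedures leave PFS and complications open to assessment by people who know, or can see, the treatment arm

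*Protocol article*

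**What the plan says.** The Randomization Procedure section of the protocol article makes one statement about blinding: "Data collection and data analysis will be blinded, except that the intervention is not blinded to participants and clinicians". Only participants and clinicians are exempted.

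Other sections describe who gathers and judges the outcomes:

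- **Clinical Data:** "Clinical data from the patients will be obtained by medical staff and recorded on an online electronic platform". The contents listed there include "laboratory examination results, imaging results, surgery details, PFS and OS". Table 3 in the same section adds operation information and postoperative pathology.
- **Follow-up:** "The patients will be followed up by researchers every month to every 3 months".
- **Study Endpoints, on adverse events:** "The investigator will determine if the adverse event is clinically significant", and "The investigators will assess possible relationships among the adverse events, the investigational drugs and the surgery".
- **Evaluation of Technology Effectiveness:** "Contrast enhanced CT and tumor marker testing were performed in the first month after D2 gastrectomy and RFA treatment", and this examination serves as the new baseline for later comparison. For ablation, "technique effectiveness is defined as no evidence of residual tumor within 1 cm of the ablation defect".

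Table 1 shows that only the test group has gastrectomy and liver radiofrequency. OS is the primary endpoint; PFS and the total complication rate are secondary. The Discussion nevertheless names OS and PFS together as the main efficacy indicators.

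**The concern.** Blinded data collection means that whoever obtains and judges an outcome does not know the arm. Here the people described as doing so are medical staff, researchers and investigators, and the material they handle reveals the operation. The statement and the procedures do not fit together.

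What is at stake is how two endpoints may be read. Identifying progression on CT, and deciding whether an event is clinically significant, both involve judgement. A reader who relies on the blinding sentence would treat PFS and complications as protected from assessment bias. For PFS this matters more than its secondary status suggests, because the Discussion puts it beside OS as a main indicator of efficacy.

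**Working it through.** No arithmetic applies: the point depends on no sample size, event count or error rate, and the plan gives no figure to reproduce. The check sets the blinding sentence against each step by which an outcome enters the record.

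1. **Who obtains the data.** Clinical Data says medical staff. If these are clinicians, they belong to the group that the blinding sentence itself exempts. The exception then covers the collectors and leaves the claim of blinded collection with little content.

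2. **What the record contains.** Imaging, surgery details and PFS sit in the same record, with operation information and postoperative pathology in Table 3. Under Table 1 only the test group is operated on, so a completed surgical field identifies the arm to anyone who fills in or reads that record. The coding described in Clinical Data restricts knowledge of patient identity. It does not conceal the arm.

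3. **What the scan shows.** The ablation criterion is applied around the ablation defect, and the new baseline is taken after gastrectomy and radiofrequency. Ablation is thus visible on test-group CT by the article's own account. That the resection is visible too follows from the treatment. Whoever reads a post-treatment scan can therefore recognise the arm.

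4. **How complications are judged.** Study Endpoints runs the postoperative window of 30 days from the procedure and lists anastomotic leak and duodenal blow-out, which presuppose surgery. The investigator decides whether an event is clinically significant and relates events to the drugs and the surgery. That last judgement cannot be made without knowing what treatment was given.

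5. **OS.** Whether and when a patient died is not a reader's judgement, so steps 1 to 4 bear little on it.

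6. **Analysis.** No section says which fields the analyst receives. The statement that data analysis is blinded is therefore not contradicted.

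Steps 1 to 3 bear on PFS, and steps 1, 2 and 4 on complications. No section describes a masked reader or an adjudicator for either endpoint.

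**The case against.** The strongest reply is that the sentence discloses the openness itself, since it says participants and clinicians are not blinded. A reader might infer that the article hides an open-label design; it does not. This part of the reply stands. The fault is that the exception empties the first half of the sentence.

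A second reply is that the article uses the terms medical staff, researchers and investigator, never says treating staff, and names nobody as the reader of CT for progression. The full protocol, not shown here, might provide an independent reader. This also stands as a limit: that progression is called by the treating team is an inference. It does not remove the conflict, because the printed sentence disagrees with the printed procedures, and an ablation defect or resected stomach stays visible to an independent reader.

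Third, the ablation criterion defines technique effectiveness in the test group, not PFS. That is correct. It shows that the scan reveals the arm; it does not show how progression is dated. Nothing printed dates PFS by tumour markers or clinician opinion, so the point cannot rest on that.

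Fourth, some complications have stated criteria, such as CT confirmation of respiratory complications and Clavien-Dindo grading, and the postoperative component can arise only in the test group, so no blind could make it comparable. This narrows the exposure, mainly to chemotherapy side effects and the clinical-significance judgement, without ending it.

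**Conclusion.** The point holds in a limited form. The claim of blinded data collection is wrong as written for both secondary endpoints, PFS and the total complication rate. OS is little affected. The conclusion assumes that medical staff and investigators know the treatment given, which the blinding sentence concedes for clinicians and the causality judgement requires for investigators.

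Two stronger readings are tempting and unsupported:

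- **That the analyst's blind fails as well.** This would require the analyst to hold the surgical fields, which no section says.
- **That the size of the bias can be stated.** It cannot be taken from the size of the test group: the termination criteria foresee patients who cannot be operated on, and these would have no operation record. Nor can it be taken from the imaging interval. The article gives that as every 3 months in Clinical Data and Follow-up but every 2 to 4 months under Evaluation of Technology Effectiveness, and it gives no frequency or direction of doubtful readings.

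The effect is therefore on what PFS and complications can support as evidence, not on a number in the plan. A correction is worth making because it is cheap and because the Discussion gives PFS a main role.

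**What to change.** Replace the blinding sentence in Randomization Procedure with wording such as:

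*The trial is open-label. Data collection and the assessment of PFS and complications are not blinded. The statistician works with coded arm labels, and the operation, ablation and pathology fields are withheld until the primary OS analysis is fixed.*

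Report PFS and complications as open-label assessments that are open to assessment bias, and rest the efficacy conclusion on OS. Bring the Discussion, which now pairs OS with PFS, into line. Analyses that need surgical data, such as the subgroup with delayed postoperative treatment in Study Endpoints, would follow once the OS analysis is fixed.

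The cost is a stated property less favourable than the present one, and the preparation of a coded data extract. No extra patients, visits or readers are needed.

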### Treatment Protocols

All eligible patients will be randomly divided into a test group or a control group according to a 1:1 distribution ratio. The test group will receive D2 gastrectomy plus liver radiofrequency plus postoperative chemotherapy. In the test group, only open surgery is allowed. The control group will receive chemotherapy alone. The chemotherapy regimens of the two groups are the same (11), S-1 plus cisplatin. S-1 will be given orally 80-120 mg/m² per day for the first 3 weeks of every 5-week cycle. The dose of S-1 will be given according to the patients’ body surface area (less than 1.25 m², 80 mg; 1.25–1.5 m², 100 mg; and greater than 1.5 m², 120 mg). Patients will receive cisplatin 60 mg/m² on Day 8 of every 5-week cycle *via* intravenous infusion. **Table 1** shows the treatments applied in this study. **Table 2** shows the medication and usage in this experiment. Because all enrolled patients are tested for the molecular profile of the tumors, such as HER2, PDL1, MSI and MMR expression, follow up treatment protocols could be adjusted according to the patients’ molecular profile, such as trastuzumab or immunotherapeutic antibody. Accordingly, in the statistical analysis of data, different patients also require conduct subgroup hierarchical analysis according to the molecular detection results of tumors to reduce data error.

**Table 1 T1:** The treatments applied in this study.

	gastrectomy (total gastrectomy, distal or proximal gastrectomy plus D2 lymph node dissection)	liver radiofrequency	chemotherapy (S-1 + cisplatin)
test group	√	√	√
control group	—	—	√

**Table 2 T2:** The medication and usage in this experiment.

Chemotherapy drugs	dose	Timing of the drugs (a total of 35 days/cycle)			
		Day 1-7/cycle	Day 8/cycle	Day 9-21/cycle	Day 22-35/cycle
S-1	80-120 mg/m² (oral)	√	√	√	—
cisplatin	60 mg/m² (intravenous infusion)	—	√	—	—

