### Study Endpoints

In this study, the primary endpoint will be the OS. The secondary endpoints PFS and total complication rate. The total complications will include postoperative and chemotherapy complications. Postoperative complications were defined as events occurring within 30 days after the procedure, the severity of which was assessed by the ClavienDindo classification system (23, 24). Postoperative complications will include surgical site infection (SSI refers to the infection that occurs in the incision, deep organ or cavity during the perioperative period. It is mainly divided into superficial wound tissue infection, deep wound tissue infection and organ/cavity infection); anastomotic leaks and duodenal blow-out (identified clinically or radiographically); Chylous fistula (defined as milky white liquid in peritoneal drainage fluid after the start of enteral nutrition); respiratory complications (defined as clinical manifestation of pneumonia or bronchopneumonia confirmed by computed tomographic scan); and other complications (such as: delayedgastricemptying, intestinal obstruction, anastomotic and/or abdominal bleeding, abdominal abscess, pancreatic fistula, pancreatitis and so on.). Postoperative mortality was defined as all-cause death occurring within 30 days after the procedure. Chemotherapy complications refer to the side effects of chemotherapy, such as ototoxicity and nephrotoxicity. For those patients delayed postoperative systemic radiotherapy and/or chemotherapy after 4 weeks of surgery due to surgery and its complications, their clinical data were recorded in detail and analyzed by subgroup stratification.

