### Monitoring of the Study

Before the start of the study, the personnel of the project unit will visit all of the research centers and discuss with the researcher (and/or other research-related personnel) the responsibility of the researcher for the research program and the responsibility of the project undertaking unit or representative.

During the study period, the project undertaker or the supervisor representing the project undertaker will regularly contact the research center for a number of reasons, including the following: providing information and technical support; establishing randomized grouping as required; confirming that the investigator complies with the study plan, that the data on the CRFs are accurately recorded, and the dosage of drugs being used is checked; and carrying out original data analysis (e.g., the data on CRFs are related to the records of patients in the hospital, and the research will compare these with other records). This requires direct access to the original records of each patient (e.g., clinical charts).

The interim analysis will be performed when half of the planned sample size is enrolled. The prespecified stopping criteria in the study protocol are as follows: if D2 gastrectomy plus liver radiofrequency combined with chemotherapy is superior to chemotherapy alone, and the analysis is statistically significant, study termination will be considered, and subsequent patients will receive D2 gastrectomy plus liver radiofrequency combined with chemotherapy. However, if the efficacy of D2 gastrectomy plus liver radiofrequency combined with chemotherapy is not superior to chemotherapy alone, and the analysis results are statistically significant, the study will be considered as invalid and the subsequent enrolled patients will receive chemotherapy alone. The Data and Safety Monitoring Committee of the China Clinical Trial Registry independently reviewed the interim analysis protocol and may decide to terminate the study early with the approval of the ethics committee of each center.

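### The S-1 dose is printed per m² in the text and in Table 2, but the dosing rule is a flat 80, 100 or 120 mg by body surface area band

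*Protocol article*

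**What the plan says.** Under Treatment Protocols, the protocol article gives both arms S-1 plus cisplatin: "The chemotherapy regimens of the two groups are the same". It states the S-1 dose in three places.

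- Running text: "S-1 will be given orally 80-120 mg/m² per day for the first 3 weeks of every 5-week cycle".
- The next sentence, which sets the dose by BSA: "less than 1.25 m², 80 mg; 1.25–1.5 m², 100 mg; and greater than 1.5 m², 120 mg". These are flat amounts in mg, with neither a per-m² unit nor a time unit.
- Table 2, S-1 row: "80-120 mg/m² (oral", without the bands. The cisplatin row directly below reads "60 mg/m² (intravenous infusion", in agreement with the text.

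Nothing elsewhere in the article reconciles the per-m² range with the flat bands.

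**The concern.** A dose per m² has to be multiplied by the patient's BSA. A banded dose has BSA built in already. The article prints the same numbers, 80 to 120, both ways, and both cannot be right.

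The drug is cytotoxic and is given in both arms of a multicentre trial. Table 2 is where a site would naturally look up a dose. It carries only the per-m² figure, next to a drug that really is dosed per m², so nothing there warns the reader. The literal reading never gives less than the band dose, so the error runs only towards overdose.

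At stake are patient safety and a uniform regimen across sites. There is also a link to the total-complication endpoint, which counts chemotherapy toxicity (Study Endpoints: "Chemotherapy complications refer to the side effects of chemotherapy, such as ototoxicity and nephrotoxicity"), but the article does not allow the effect on that endpoint to be quantified.

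**Working it through.** **Inputs from the article (Treatment Protocols and Table 2)**

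- Printed range: 80 to 120 mg/m² per day.
- Band dose D: 80 mg if BSA < 1.25 m²; 100 mg if 1.25 to 1.5 m²; 120 mg if > 1.5 m².
- S-1 days per cycle, from Table 2: days 1–7, 8 and 9–21, so 21 days.

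**Assumption.** The article gives no BSA distribution. I take 1.2 to 2.0 m² and vary it below.

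**Step 1: can the printed range be reproduced from the bands?** As flat amounts, the lowest band is 80 mg and the highest 120 mg, which matches 80 to 120 mg exactly. Per m², the band dose is D / BSA. This runs from 120 / 2.0 = 60 mg/m² to 100 / 1.25 = 80 mg/m². It equals 80 only at 1.25 m², approaches 80 just above 1.5 m², and is lower everywhere else. The bands therefore do not reproduce 80 to 120 mg/m².

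**Step 2: how far does the literal reading exceed the bands?** Literal dose = 80 × BSA to 120 × BSA. Ratio = literal dose / D.

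| BSA (m²) | Band dose (mg/day) | Band dose per m² | Literal dose (mg/day) | Ratio |
|---|---|---|---|---|
| 1.20 | 80 | 66.7 | 96–144 | 1.20–1.80 |
| just under 1.25 | 80 | 64.0 | about 100–150 | 1.25–1.875 |
| 1.25 | 100 | 80.0 | 100–150 | 1.00–1.50 |
| 1.40 | 100 | 71.4 | 112–168 | 1.12–1.68 |
| 1.50 | 100 | 66.7 | 120–180 | 1.20–1.80 |
| 1.51 | 120 | 79.5 | 120.8–181.2 | 1.01–1.51 |
| 1.60 | 120 | 75.0 | 128–192 | 1.07–1.60 |
| 1.80 | 120 | 66.7 | 144–216 | 1.20–1.80 |
| 2.00 | 120 | 60.0 | 160–240 | 1.33–2.00 |

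The ratio rises with BSA within each band, so its extremes lie at the band ends and at the limits of the assumed range. Overall it is 1.0 (80 mg/m² at 1.25 m²) to 2.0 (120 mg/m² at 2.0 m²).

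**Step 3: per 21-day course.**

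- 1.6 m²: 21 × 120 = 2,520 mg by band; 21 × 128 = 2,688 to 21 × 192 = 4,032 mg literally.
- 2.0 m²: 2,520 mg by band; 21 × 160 = 3,360 to 21 × 240 = 5,040 mg literally.

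**Step 4: other BSA ranges.** For 1.1 to 1.9 m² the ratio is 1.0 to 1.9. For 1.3 to 2.2 m² it is 1.0 to 2.2. Only the upper end depends noticeably on the assumption.

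**The case against.** The best reply is that the operative rule comes straight after the faulty sentence. A range alone does not tell a prescriber which value to use, and the only selector printed is the band rule, which is in flat mg. A careful reader of the whole paragraph should reach the right dose. That stands, and it is why the bands are taken here as the intended dose. It does not repair Table 2, which omits the bands. Nor does it rule out using the bands to choose a value within the per-m² range. At 1.6 m² that would give 120 × 1.6 = 192 mg instead of 120 mg. The band sentence also takes its per-day basis from the faulty sentence, so that sentence cannot simply be ignored.

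Further points against a high rating:

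- **The factor of 2.0 is a corner case.** It needs the top of the printed range and the top of the assumed BSA range together. This stands. At the bottom of the printed range the excess over 1.2 to 1.8 m² is at most 25%, and at exactly 1.25 m² there is none.
- **Safeguards exist.** Monitoring of the Study says that "the dosage of drugs being used is checked", Clinical Data and Follow-up provide for at least monthly clinical and laboratory checks, and patients with serious toxicity leave the study. These help only in part: the article does not say which dose statement monitors check against, and toxicity checks act after exposure.
- **The article condenses a fuller protocol.** The sites' dosing instructions may be correct, and no misdosing is shown. This stands, but the published dose is a wrong statement, not a detail left to another document.

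**Conclusion.** The concern holds. The per-m² unit on S-1 appears to be an error, printed in both the text and Table 2, and it contradicts the band rule beside it. Over an assumed BSA of 1.2 to 2.0 m², the literal reading gives 1.0 to 2.0 times the band dose and never less than it. That the bands are the intended dose is an inference from the matching end points (80 and 120) and from their being the only complete rule; it needs clinical confirmation.

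This must be corrected on safety grounds alone. Because the arms share the same regimen text, the error does not by itself bias the comparison of overall or progression-free survival. There is no evidence in the article that any patient was dosed per m².

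**What to change.** First have the responsible clinicians and pharmacy confirm that the bands are the intended daily dose. Then:

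1. In the Treatment Protocols text, state S-1 as 80–120 mg per day according to BSA band, without the per-m² unit.
2. Replace the S-1 dose cell in Table 2 with the bands: BSA under 1.25 m², 80 mg/day; 1.25 to 1.5 m², 100 mg/day; over 1.5 m², 120 mg/day. Leave cisplatin at 60 mg/m².
3. Notify all sites of the correction, and tell monitors that the bands are the dose to check against.

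The cost is one sentence, one table cell and a note to sites and monitors. Sample size, endpoints and analysis do not change.
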